## **2. Participant transitioned to moderate withdrawal or greater within 4 hours of the XR-BUP injection**

- Transition to moderate withdrawal is defined as achieving a COWS score of 13 to 24 (inclusive). This is measured at 30, 60, 90, 120, 150, 180, 210, and 240 minutes post injection. If at least one post-baseline measurement is greater than or equal to 13, the participant meets this criterion.
- In order for this outcome to be evaluable (i.e., non-missing), a participant must have one pre-injection (baseline) COWS score and at least two post-injection COWS scores, one of which is collected within the last hour of the 4-hour period after the injection. If a participant only has one post-injection COWS score which indicates transition to moderate withdrawal or greater, this outcome is considered evaluable (as having met the criterion for this outcome).

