##### **3.1.1.10 Baseline COWS Score**

The baseline COWS score is defined as the COWS score entered on the COW eCRF at the baseline/pre-injection visit after enrollment (visit B000). If this is not available because less than 30 minutes elapsed from the baseline/pre-injection visit and the COWS score completed to determine eligibility (as indicated by the CONOBLCW variable on the COW eCRF), then the COWS score entered on the COW eCRF at the screening visit (visit A1) is the baseline COWS score. Otherwise, the baseline COWS score is missing.

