## **3. Participant experienced a precipitated withdrawal within 1 hour of XR-BUP injection**

- Potential precipitated withdrawal events are adjudicated by study consultants and captured on the PWD eCRF as 'Yes' or 'No' at 240 minutes after the XR-BUP injection. If the time listed for this precipitated withdrawal is within 1 hour of the time of XR-BUP injection (including exactly 1 hour), the participant is considered to have experienced this outcome.
- In order for this outcome to be evaluable (i.e., non-missing), the PWD eCRF must be completed with a time of precipitated withdrawal provided one occurred.

For all three outcome measures, if the outcome measure is not evaluable (i.e., missing), the worst-case scenario will be imputed for that outcome measure where the participant is assumed to have experienced the outcome measure.

The *a priori* conditions on these outcomes in the Primary Ancillary Analysis population to inform expanding enrollment in the RCT component are:

- <20% of participants will experience a 5 or greater increase in COWS score within 4 hours of injection
- <10% of participants will transition to moderate withdrawal (COWS score 13 to 24, inclusive) within 4 hours of injection
- <10% of participants will experience precipitated withdrawal within 1 hour of injection

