### 7.1.4 Missing Data Analysis

Missing data for the primary outcome measures are handled in a worst-case scenario as described in Section 7.1.1.

Other methods of handling missing data, including a complete-case analysis and best-case (where missing outcomes are imputed as the participant not experiencing the outcome) scenarios may be conducted if any primary outcome measures are missing.

Sensitivity analyses (complete-case and best-case), analogous to those for the primary outcome, will be presented if more than 5% of the primary outcome measures are missing for the Full Ancillary Analysis Population.

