|                                                                 | < 4 and no    |                 |                                                                                                                             |                                                                                                                    |                                                                                                                     |
|                                                                 | < 4 and yes   |                 |                                                                                                                             |                                                                                                                    |                                                                                                                     |

Participants with missing values for COWS scores or precipitated withdrawals are imputed as having experienced the event.

 Calculated using the exact Clopper-Pearson method.

 One participant in the Full Ancillary Analysis Population had a missing COWS score at baseline.

 Eligibility criteria were updated with protocol version 4.0. The following changes were made: (i) patients with urines that were only positive for fentanyl on the point of care test strip were eligible if their clinical history and physical exam were consistent with opioid use and they met DSM-5 criteria for moderate to severe OUD; (ii) having an index ED visit due to opioid overdose was no longer considered an exclusion criteria; and (iii) the definition of current enrollment in the exclusion criteria of formal addition treatment was changed from 14 to 7 days.

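### SAP 7.1.1 lets a missing baseline override observed COWS scores for ancillary outcome 2, and its exceptions, read literally, remove some observed events from the sensitivity analyses

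*Combined protocol and SAP*

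**What the plan says.** SAP 7.1.1 sets three ancillary primary outcomes. Outcome 2 is transition to moderate withdrawal within four hours of the XR-BUP injection, from COWS scores at eight post-injection times (30 to 240 minutes). It is scored as follows: "If at least one post-baseline measurement is greater than or equal to 13, the participant meets this criterion". The baseline does not enter.

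The evaluability rule for the same outcome does use it: "In order for this outcome to be evaluable (i.e., non-missing), a participant must have one pre-injection (baseline) COWS score and at least two post-injection COWS" readings; one reading must also fall in the final hour of observation. There is one exception: "If a participant only has one post-injection COWS score which indicates transition to moderate withdrawal or greater, this outcome is considered evaluable". Outcome 1 (a rise of 5 or more) has the same rule and a parallel exception, for a participant with one baseline and one post-injection score that together show the rise.

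For a non-evaluable outcome, "the worst-case scenario will be imputed for that outcome measure where the participant is assumed to have experienced the outcome measure". SAP 7.1.4 adds complete-case and best-case analyses, the latter being one "where missing outcomes are imputed as the participant not experiencing the outcome".

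SAP 3.1.1.10 takes the baseline from the pre-injection visit. The screening score replaces it only when the pre-injection score was omitted because less than 30 minutes had passed since the eligibility score. "Otherwise, the baseline COWS score is missing".

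Under SAP 7.1.2 an a priori condition is met when the upper limit of the exact two-sided 95% interval, in the first 75 participants, is below the threshold. For outcome 2 the threshold is 10%.

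**The concern.** Worst-case imputation is a sound choice when the outcome is unknown. For outcome 2 with a missing baseline, nothing needed to score it is missing: eight scores below 13 show that the participant did not have the event, yet the rule records one. The primary estimate of a safety outcome would then include an event that the data contradict.

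The second problem runs the other way. The exceptions are meant to keep an observed event when follow-up is thin, but they are worded for a single post-injection score. A participant with two or more scores, one of them qualifying, and none in the last hour meets neither the main rule nor the exception. The worst-case primary analysis still counts the event. The complete-case analysis loses it and the best-case analysis reverses it, although the event was seen.

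**Working it through.** **1. Reproduce the SAP's figures.** With x = np events, the Clopper-Pearson limits are the 2.5% quantile of Beta(x, n − x + 1) and the 97.5% quantile of Beta(x + 1, n − x). At n = 75 and p = 0.01, 0.05, 0.10, 0.15, 0.20, 0.25 and 0.30, the widths are 0.0664, 0.1134, 0.1485, 0.1732, 0.1918, 0.2062 and 0.2173. The table in SAP 10.1 gives 0.066, 0.113, 0.148, 0.173, 0.192, 0.206 and 0.217, which agree within rounding.

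**2. Apply the rules of SAP 7.1.1 literally.** The patterns below are constructed and are not trial data. The last hour is taken as 180 to 240 minutes. No baseline means that the pre-injection score is absent without the under-30-minute reason.

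| Pattern | Outcome | Observed | Evaluable | Primary (worst case) | Complete case | Best case |
|---|---|---|---|---|---|---|
| A: no baseline; eight scores, all 6 | 2 | non-event | no | event | excluded | non-event |
| B: no baseline; eight scores, 15 at 60 min, the rest 6 | 2 | event | no | event | excluded | non-event |
| C: no baseline; a single score of 15 | 2 | event | yes | event | event | event |
| D: baseline 5; 9 at 30 min, 15 at 60 min, nothing later | 1 and 2 | event (rise of 10; score above 12) | no | event | excluded | non-event |
| E: baseline 5; 15 at 30 min only | 1 and 2 | event | yes | event | event | event |
| F: baseline 3; 5 at 30 min, 9 at 60 min, nothing later | 1 | event (rise of 6) | no | event | excluded | non-event |

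A is the false event in the primary analysis. B against C, and D against E, show that a participant with more data can be classified worse than one with less. The footnote to SAP Table 12 supports the strict reading: it requires a pre-injection COWS and two post-injection scores, one in the last hour.

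Outcome 1 is different. Without a baseline the rise cannot be computed, so worst-case imputation there does not override an observation. For outcome 1 only the exception is at fault, and it leaves the primary count unchanged.

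**3. What one false event would use up.** Upper limits at n = 75:

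- 2 events: 9.30%, so the 10% condition is met.
- 3 events: 11.25%, so it is missed.

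Two events are therefore allowed, and one participant scored as in pattern A would take one of them.

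**4. Conditional size.** Assume that exactly one of the 75 is in pattern A and that the other 74 have a true event rate p. The documents give no p; 1% and 2% are illustrative. The chance of meeting the condition is P(X ≤ 2 | 75, p) without such a participant and P(X ≤ 1 | 74, p) with one.

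- p = 2%: 0.810 falls to 0.563.
- p = 1%: 0.960 falls to 0.831.

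**The case against.** **The error is conservative.** In a safety gate, worst-case scoring is deliberate, and here it can only overstate harm. That stands as to direction. It does not justify imputing an outcome that was observed.

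**The exception can be read generously.** The scoring sentence says that one score of 13 or more is enough, so the exception may only have been meant to confirm that a single score suffices. That is a fair reading of outcome 2, but the evaluability rule and the Table 12 footnote point the other way, and two programmers could code it differently. The effect is also limited. The complete-case and best-case analyses are optional unless more than 5% of the primary outcome measures are missing in the full population. For participants with a baseline, rises of 5 or more are highlighted in the plot under SAP 8.1.2.

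**A reader might infer that someone has already been mis-scored**, because a footnote to SAP Table 16 says: "One participant in the Full Ancillary Analysis Population had a missing COWS score at baseline". The documents do not support this. That population is everyone who consented (SAP 3.1.1.3), about 100 people and not only the first 75. It can include people who were never injected, since Listing 1 has a column for receipt of the injection. Nothing shows that this participant was injected, had post-injection scores or was among the 75.

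**A reader might infer that one participant could block expansion of the RCT.** Under protocol 8.10 and SAP 11.2, missing a condition sends the data to the DSMB for a recommendation. The DSMB had already agreed in May 2021 to admit COWS 4–7.

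**A reader might infer that the screening COWS should always stand in for a missing baseline**, since COWS below 8 is an entry criterion. SAP 3.1.1.10 limits that substitution to a recent score, and outcome 1 is a change score. No maximum interval from screening to injection is stated, so a score of any age could misclassify the rise.

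**Conclusion.** Both defects follow from the text. The baseline requirement for outcome 2 turns an observed non-event into a primary-analysis event. The exceptions for outcomes 1 and 2, read literally, let an observed event drop out of the complete-case analysis and become a non-event in the best-case analysis, in conflict with the SAP's own scoring sentence for outcome 2.

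The size is conditional. If one injected participant among the first 75 were affected by the baseline rule, one of the two events allowed under the 10% limit would be used. The falls in probability under working step 4 assume exactly one such participant and are not an expected effect of the rule. The documents do not show that any exists. The primary error overstates harm, and the decision to expand the RCT has been taken. What is at stake is a correct final estimate and sensitivity analyses that respect the recorded data.

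**What to change.** 1. In SAP 7.1.1, remove the pre-injection COWS from the evaluability rule for outcome 2, and adjust the Table 12 footnote to match.
2. Reword both exceptions so that any participant with at least one post-injection score meeting the criterion (for outcome 1, with a baseline available) is evaluable as an event in all analyses, however many scores there are and whenever they were taken. Apply worst-case and best-case imputation only to the rest.
3. Report the estimates under the current rule beside the corrected ones. Ancillary results went to the DSMB in April 2021, and the first change can only lower the outcome 2 count, so a silent replacement would look results-driven.
4. Leave SAP 3.1.1.10 as it is for the primary definition. Using the screening COWS as baseline regardless of its age should be at most a labelled sensitivity analysis for outcome 1.

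The cost is a few sentences in the SAP, a small programming change, and one extra set of estimates with a note on when and why the rule changed.

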## **3. Participant experienced a precipitated withdrawal within 1 hour of XR-BUP injection**

- Potential precipitated withdrawal events are adjudicated by study consultants and captured on the PWD eCRF as 'Yes' or 'No' at 240 minutes after the XR-BUP injection. If the time listed for this precipitated withdrawal is within 1 hour of the time of XR-BUP injection (including exactly 1 hour), the participant is considered to have experienced this outcome.
- In order for this outcome to be evaluable (i.e., non-missing), the PWD eCRF must be completed with a time of precipitated withdrawal provided one occurred.

For all three outcome measures, if the outcome measure is not evaluable (i.e., missing), the worst-case scenario will be imputed for that outcome measure where the participant is assumed to have experienced the outcome measure.

The *a priori* conditions on these outcomes in the Primary Ancillary Analysis population to inform expanding enrollment in the RCT component are:

- <20% of participants will experience a 5 or greater increase in COWS score within 4 hours of injection
- <10% of participants will transition to moderate withdrawal (COWS score 13 to 24, inclusive) within 4 hours of injection
- <10% of participants will experience precipitated withdrawal within 1 hour of injection

### **7.1.2 Analysis of the Primary Outcome Measures**

Each of the three primary outcome measures will have the percent (as proportions) of the Primary Ancillary Analysis population experiencing the outcome estimated. A 95% confidence interval, calculated by the Exact Clopper-Pearson method, will also be provided for each outcome measure. The following is template SAS code to generate the proportions and confidence intervals:

```
proc freq data = dat;  
    table outcome / binomial(cl=exact level='1') alpha=0.05;  
run;
```

where `dat` is the name of the dataset with one row per participant and `outcome` is the name of any of the outcomes above coded as '0' for not experiencing and '1' for experiencing the outcome.

If the upper limits of the above confidence intervals are less than the *a priori* condition on the outcome (Section 7.1.1) in the Primary Ancillary Analysis population, the *a priori* condition is considered achieved.

A listing will be provided of participants that experienced at least one of the outcomes to present which participants experienced any combination of the primary outcome measures.

The summary table of primary outcomes is presented overall and not by site.

The availability of data to compute the primary outcomes will be summarized by site.

### 7.1.3 Supportive Analyses of the Primary Outcome Measures

The three primary outcome measures will be computed for the Full Ancillary Analysis population.

The proportions and confidence intervals for each of the primary outcome measures will be estimated in the following subgroups of both the Primary Ancillary Analysis and Full Ancillary Analysis populations:

- 1) Participants enrolled before or after eligibility changes in protocol version 4.0
  - If the ENRC eCRF for a participant was completed with form version 1.0, the participant was enrolled before eligibility changes. If it was completed with a later form version, the participant was enrolled after the eligibility changes.
- 2) Participants with a baseline COWS score between 4 and 7 (inclusive) or less than 4
  - Baseline COWS score is defined as in Section 3.1.1.10.
- 3) Participants positive for fentanyl at baseline on the UDS eCRF
- 4) All four combinations of the subgroups in 2) and 3) on baseline COWS and baseline fentanyl

Subgroup analyses for sex, race, ethnicity, and age will be performed as required by the NIH (NIH, 2016). The proportions and confidence intervals for each of the primary outcome measures will be estimated in the following subgroups for the Full Ancillary Analysis population:

- 1) Males and females
- 2) Black, white, and all other races
- 3) Hispanic and non-Hispanic participants
- 4) Participants older than the median age and those equal to or younger than the median age.

The SAS code noted above will be used to generate the proportions and confidence intervals in the subgroups. Subgroups will be created with a 'by' statement in the 'proc freq' or by sub-setting the analysis file directly.

Summary tables of supportive analyses of primary outcomes will be presented overall and not by site.

### 7.1.4 Missing Data Analysis

Missing data for the primary outcome measures are handled in a worst-case scenario as described in Section 7.1.1.

Other methods of handling missing data, including a complete-case analysis and best-case (where missing outcomes are imputed as the participant not experiencing the outcome) scenarios may be conducted if any primary outcome measures are missing.

Sensitivity analyses (complete-case and best-case), analogous to those for the primary outcome, will be presented if more than 5% of the primary outcome measures are missing for the Full Ancillary Analysis Population.

#### **7.1.5 Additional Outcome Measures**

Two additional outcome measures, not pre-specified in the protocol, will be computed:

1. Participant experienced a 5 or greater increase in COWS score within 4 hours of the XR-BUP injection, in the absence of a precipitated withdrawal within 1 hour of the XR-BUP injection.
2. Participant transitioned to moderate withdrawal within 4 hours of the XR-BUP injection, in the absence of a precipitated withdrawal within 1 hour of the XR-BUP injection.

These outcomes will be analyzed in the same manner as the primary outcome. Tables will be generated for the Full Ancillary Analysis and Primary Ancillary Analysis populations.

#### **7.1.6 Definition of Secondary Outcome Measures**

##### **7.1.6.1 Vital Signs**

Vital signs are collected at on the VTR eCRF at baseline and 30, 60, 90, 120, 150, 180, 210, and 240 minutes post-injection. Specific measurements are blood pressure, pulse rate, respiratory rate, oxygen saturation, and temperature.

##### **7.1.6.2 Clinical Opiate Withdrawal Scale (COWS)**

COWS is collected on the COW eCRF at baseline and 30, 60, 90, 120, 150, 180, 210, and 240 minutes post injection. It is also collected at Day 7. Total values range from 0 to 48.

##### **7.1.6.3 Objective Opiate Withdrawal Scale (OOWS)**

OOWS is collected on the OOW eCRF at baseline and 30, 60, 90, 120, 150, 180, 210, and 240 minutes post injection. Total values range from 0 to 13.

##### **7.1.6.4 Adjective Rating Scale for Withdrawal (ARSW)**

ARSW is collected on the RSW eCRF at baseline and 240 minutes post-injection. The total score is between 16 and 144 defined as the sum of 16 self-reported items about how the participant is feeling. Each items has a scale of 1 (None) to 9 (Severe).

##### **7.1.6.5 Pupillary Diameter**

Pupillary diameter is collected on the PPD eCRF at baseline and 30, 60, 90, 120, 150, 180, 210, and 240 minutes post-injection. Two readings, one for each eye, are taken at each time point. The mean of the two values will be used for analysis.

##### **7.1.6.6 Craving - Desire to Use Opioids**

Desire to use opioids is collected on the CRV eCRF at baseline, 240 minutes post-injection, and daily through Day 7 via Qualtrics. The value is from a visual analog scale from 0 (definitely not) to 100 (definitely so).

##### **7.1.6.7 Bad Drug Effects**

Bad drug effects are collected on the BDE eCRF at baseline and 240 minutes post-injection. The value is from a visual analog scale from 0 (not at all) to 100 (extremely).

#### **7.1.6.8 Pain Assessment**

Pain assessment (degree of pain at the injection site) is collected on the PAR eCRF immediately following the injection and again at 30 and 240 minutes post-injection. The result is on a scale of 0 (no pain) to 10 (worst possible).

Pain is also assessed on the ISR eCRF at the Day 7 Follow-up visit on a scale from 0 (no pain) to 10 (worst possible).

#### **7.1.6.9 Local Tolerability Scale**

Local tolerability is collected on the LTS eCRF at 30 and 240 minutes post-injection. Specific measurements are erythema and swelling at the injection site. Both measurements are on a scale from 0 to 3 (0 = none, 1 = mild, 2 = moderate, and 3 = severe).

#### **7.1.6.10 Precipitated Withdrawals**

Precipitated withdrawals are collected on the PWD eCRF as 'Yes' or 'No' at 240 minutes post-injection. The time of the withdrawal is noted.

#### **7.1.6.11 Satisfaction Questionnaire**

Satisfaction is measured at Day 7 on the S99 eCRF. Overall experience with XR-BUP (S99.S9MDEVAL) is rated on a scale from 1 (completely ineffective) to 5 (completely effective). The importance of the following seven characteristics is rated on a scale from 1 (not important) to 7 (extremely important).

- Does not require daily medication
- Prevents other people from having access to my medication
- Allows me to travel without carrying medication with me
- Spares regular visits to the pharmacy to pick up prescriptions
- Prevents accidental exposure to children or pets
- Improves my privacy as a patient
- Helps me to make sure I do not miss or skip my medication doses

